### Process evaluation measures and data collection methods

The process evaluation will have four components: internal practice context; external healthcare context; implementation fidelity; and cost (see Table 3).

**Table 3 Tab3:** Process measures, data sources and timeline for data collection

Domain	Measures	Data sources	Administration
Internal practice-level context	• Staffing/FTEs • Payer mix • Patient demographics • Baseline integration practice transformation components (population management) • PCMH certification	• Practice survey • Site visits and key informant (KI) interviews with sample of providers and staff	• Surveys at baseline, 12 and 18 months • Site visits and KI interviews baseline and 12 months
External context	• Regulatory and financial environment (e.g., pay-for-performance, value based payment)	• Provider surveys • KI interviews with sample of practice site providers and staff	• Ongoing
Implementation fidelity	• PF activities: dose, intensity and mode of delivery of PF intervention Practice change: Extent to which practice change components are implemented and in use	• PF activities: Web-based PF tracking system, Webinar registration and evaluation and collaborative call attendance • Practice change: practice change survey and site visits/KI interviews	• Ongoing PF tracking using saleforce.com • Practice change survey monthly
Cost	• Implementation and intervention cost	• Cost data collection template embedded in PF tracking system	• Ongoing and reviewed monthly

#### Internal and external context

These domains will be assessed using both qualitative and quantitative data. The lead clinician or lead practice administrator will be asked to complete a survey (in addition to the survey described previously to assess primary care capacity) that will assess practice characteristics (e.g., use of EHR, FTEs, PCMH status, patient demographics). The survey will be conducted at baseline, 12 and 18 months. In order to obtain a deeper understanding of internal and external context, we will conduct semi-structured interviews with at least one provider and one staff person at 40 sites spread over different waves. We will visit half of these sites early in their implementation of the intervention and again toward the end of the intervention period. The interviews will focus on the practice-specific context, the local and state health policy environment, and experience with practice facilitation. We will visit the other 20 sites one time post-intervention. These sites will be chosen to represent variability in response to the intervention in terms of changes in patient outcomes.

To gain a broader perspective on external health care context and ongoing and emerging practice transformation programs in New York State and nationally, we will conduct semi-structured interviews with 10 key informants who represent leaders in this area from the city and state.

#### Implementation fidelity

We will assess two core measures of fidelity: (1) PF activities (i.e., to what extent is the PF protocol adhered to in terms of practice visits and provider participation in webinars and collaborative calls?) and (2) practice change (i.e., to what extent is the change package, defined primarily by CCM and PCMH, implemented as specified?).Practice facilitation activities: The primary outcome measure for PF activities is the frequency, duration, and mode of contact. PF activities are measured with data from the web-based software tool (Salesforce.com) that PCIP is currently using to track their practice facilitators’ activities. Each site has a separate page in Salesforce that includes the relevant elements for documenting PF activities and practice change components. Practice facilitators complete documentation in Salesforce after every visit including the time spent at the practice site, who the practice facilitator met with at the sites, what activities were discussed, outcomes of the visits, and agreed upon next steps (e.g., set date for upcoming visit). We will also track provider participation in other components of the PF intervention (e.g., webinars).Practice change: We will also use Salesforce to assess our targeted practice changes (e.g., use of clinical decision support). Practice facilitators complete a survey, which is embedded in Salesforce, after each visit (i.e., monthly). The survey uses a 6-point scale (not yet educated; educated/PDSA; educated/using; educated/not using/deferred; educated/not using/refused; and not applicable) to assess practice change components that are the target of the intervention and correspond to the main elements of PCIP’s QI manual, which we have mapped to CCM and PCMH [9, 10]. Facilitators will also complete monthly narrative reports that will provide an overview of all implementation activities, including perceptions about what components of the intervention did and did not work and approaches to adaptation of intervention components.

#### Cost

We will apply a practical, cost assessment methodology developed by Ritzwoller to assess the implementation costs of the intervention [37]. This approach provides data on what resources would be needed to implement and replicate the intervention. To determine the implementation and intervention costs, we will collect resource costs based on health professionals’ time requirements (including training), the facilitator’s time, IT costs, and needed supplies or equipment. We will aggregate the data across individual cost capture templates based on the tasks and timeline of the project. Intervention-specific data are defined by asking the question “would this resource be needed to deliver the intervention in practice?” After intervention specific resources are differentiated from research and development, total intervention costs per patient and per practice can be calculated. We will also conduct sensitivity analyses to estimate the range of intervention costs in a variety of settings and circumstances.

### Analysis plan

#### Aim 1

The primary outcomes are the proportion of patients who reach clinical goals based on national guidelines for (a) aspirin use, (b) HTN control, (c) blood cholesterol management, and (d) smoking cessation assistance at the end of the intervention (12 months) period and 6 months post-intervention. Each of the four hypotheses referring to the four primary outcomes will be tested separately with a two-sided test with *α* = 0.05, i.e., no adjustment for multiple testing will be applied. The analysis of effect of PF on the ABCS outcome measures in the context of a stepped-wedge design will be based on a generalized linear mixed model (GLMM). In particular, to assess the intervention effect, we will use a Poisson model with random site and provider within site effects. Each model will be as follows:1$$ \log \left({C}_{it}\right)=\mu +{\beta}_1t+{\beta}_2{I}_{it}^{PF}+{\beta}_3{I}_{it}^{PF}\left(t-{s}_i\right)+\gamma {Z}_i+{b}_i+ \log \left({E}_{it}\right), $$

where *C*
_*it*_ is the number of patients in site *i* who (a) had received aspirin, (b) had controlled blood pressure, (c) had controlled cholesterol, or (d) received smoking cessation counseling during period *t*, for *t* ∈ (0, 1, …, 11). Each period is 3 months, and *t* = 0 is the baseline quarter. *I*
_*it*_^PF^ is an indicator variable, and *I*
_*it*_^PF^ = 1 if site *i* has been assigned to the PF intervention at period *t*, *I*
_*it*_^PF^ = 0 otherwise. *s* is the time period when the PF intervention begins for site *i. Z* is a site-level indicator variable, *Z* = 1 if site *i* has three or more providers, *Z* = 0 otherwise. *E*
_*it*_ is the number of patients at site *i* who were eligible to be counted during period *t*. The eligible pool of patients *E*
_*it*_ will be different for each outcome and has been described in detail in Table 1. Log(*E*
_*it*_), considered the “offset” in the Poisson regression model, is a random effect for site *i* with mean 0 and variance *σ*
_*b*_^2^. The estimation via model (1) takes into account a general time trend and allows for the intervention effects to grow over time following implementation of the intervention.

Our primary outcome of interest for each of the four models is proportion of patients who meet clinical goals (described above) at 12 months. In each model, this effect (after taking into account general time trends) would be captured by *β*
_2_ + 3*β*
_3_. For the four primary outcomes, we will conduct tests with these null and alternative hypotheses: *H*
_0_ : *β*
_2_ + 3*β*
_3_ = 0 vs. *H*
_*A*_ : *β*
_2_ + 3*β*
_3_ ≠ 0. The models will be fit using the LME4 package using R software.

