### Study design

HHNYC is a stepped-wedge cluster randomized controlled trial that is designed to evaluate the implementation process and the impact of PF (intervention) compared to usual practice (control), on implementation of the Million Hearts ABCS treatment guidelines in 250 primary care practices. All practice sites begin as part of the control condition and are block-randomized into four waves with each wave beginning 3 months after the start of the prior wave and lasting for 12 months (see Table 1). All clusters eventually receive the intervention, and outcomes will be measured every 3 months in all clusters. We anticipate, conservatively, a 15 % attrition rate; therefore, we have enrolled 290 sites to ensure that enrollment of the required 250 sites is achieved at the end of the study. This study has received Institutional Review Board approval by the New York University School of Medicine.

**Table 1 Tab1:** Stepped-wedge study design

	Year 1 (months)				Year 2 (months)				Year 3 (months)			
Clusters	3	6	9	12	15	18	21	24	27	30	33	36
	Time period											
1 (80 sites)		C	X	X	X	X	F	F				
2 (70 sites)		C	C	X	X	X	X	F	F			
3 (70 sites)		C	C	C	X	X	X	X	F	F		
4 (70 sites)		C	C	C	C	X	X	X	X	F	F	

*C* control period, *X* intervention period, *F* follow up period

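### Model (1) does not say how the two follow-up quarters per wave are handled and has no term for them, so the 6-month post-intervention effect is extrapolated or set to zero, and the 12-month contrast can be biased towards the null

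*Protocol article*

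**What the plan says.** The first sentence of Aim 1 in the Analysis plan places the primary outcomes at two times, "at the end of the intervention (12 months) period and 6 months post-intervention". A later sentence narrows the focus: "Our primary outcome of interest for each of the four models is proportion of patients who meet clinical goals (described above) at 12 months". The 12-month effect is then given as a contrast: "this effect (after taking into account general time trends) would be captured by" β2 + 3β3. The only null hypothesis is that this sum is zero, tested for each of the four outcomes at two-sided 0.05.

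Model (1) contains a linear term in period t, an indicator that is 1 if the site "has been assigned to the PF intervention at period" t, and a linear slope in t − s that applies while the indicator is 1. The text says this form "allows for the intervention effects to grow over time following implementation of the intervention". Period t runs from 0 to 11.

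Table 1 in Study design distinguishes three states: control (C), intervention (X) and follow-up (F). The same section says: "All clusters eventually receive the intervention, and outcomes will be measured every 3 months in all clusters". The section on outcome measures and Table 2 confirm that outcome data are collected to 6 months after the intervention.

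**The concern.** The design has three states and the model has two. The plan does not say whether an F quarter has indicator 1, has indicator 0, or is left out, and each choice means something different.

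- **Indicator 1 in F.** Both F quarters must lie on the straight line fitted through the four X quarters. A plateau or a loss after facilitation ends cannot show as such. It flattens β3 and lowers the 12-month contrast.
- **Indicator 0 in F.** Post-intervention quarters are counted as control. Any persisting benefit is absorbed into the time trend and taken away from the intervention effect.

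The issue affects the 12-month test of all four primary outcomes. It also affects what can be said about sustainability six months after facilitation ends, which the plan lists among the primary outcome times.

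**Working it through.** **Extent of F.** From Table 1, waves 1 to 4 have 1, 2, 3 and 4 C quarters, then 4 X and 2 F quarters each. That is 10 C + 16 X + 8 F = 34 wave-quarters, so 8 of 34 are F. The filled columns run from month 6 to month 33, ten quarters, which fit inside the twelve values of t. No exclusion of F is stated.

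**Calibration to the plan's own power figure.** The Appendix claims over 80% power for 20.0% to 22.2% (ratio 1.11), with 50 eligible patients per physician, 63 sites per wave and between-site variance 0.10. It does not give physicians per site. An analytic calculation for the Appendix contrast β2 + 2β3 gives 60–62% with 1 physician per site, 74–76% with 1.5, 84–85% with 2 and 94–95% with 3. At 2 per site the other Appendix figures are also close: 93–94% against the stated 92% for 70 patients, and 89–90% against the stated 91% for a 25% baseline. I therefore assume 2 physicians per site, or 2 × 50 × 0.20 = 20 expected events per site-quarter.

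**Projection.** The noise-free log-mean pattern y is fitted by weighted least squares to model (1) without the practice-size covariate:

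b = (Σ n X′V⁻¹X)⁻¹ Σ n X′V⁻¹y, with V = (1/20)·I + 0.10·J (I the identity matrix, J all ones) and n = 63 sites per wave.

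Let L = log(1.11) = 0.104. The true effect in the four X quarters is L/4, L/2, 3L/4 and L, with no background trend. The F trajectory is an assumption, because the document gives none. Recovery is (b2 + 3b3)/L, with the fitted ratio in brackets.

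| Effect in the two F quarters | F coded 1 | F coded 0 | F left out | X-only terms plus two F indicators |
|---|---|---|---|---|
| Growth continues on the line | 100% (1.110) | −3% (0.997) | 100% | 100% |
| Gain held at L | 83% (1.090) | 25% (1.027) | 100% | 100% |
| Falls to L/2, then 0 | 49% (1.052) | 82% (1.090) | 100% | 100% |
| Lost at once | 38% (1.041) | 100% (1.110) | 100% | 100% |
| SE of 12-month contrast | 0.0429 | 0.0142 | 0.0446 | 0.0441 |

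The percentages do not depend on the size of the ratio. With waves of 80/70/70/70, 10 events per site-quarter and a ratio of 1.10, the held-gain figures are 83% (coded 1) and 26% (coded 0).

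**Shape of the build-up.** With F coded 1 and half of the effect immediate, recovery is 89% (held) and 54% (fading). For a pure step that is held it is 100%. With F coded 0 and the gain held, it stays at about 25% for every split tried.

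**Six-month effect, F coded 1.** β2 + 5β3 gives 1.127 against a true 1.110 if held, and 1.046 against a true 1.000 if fading.

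**Effect on the 12-month test.** Wald power is Φ(fitted effect/SE − 1.96):
- With F indicators: 0.104/0.0441 = 2.37, about 66%.
- F coded 1, gain held: 0.83 × 0.104/0.0429 = 2.02, about 52%.
- F coded 1, gain fading: 0.49 × 0.104/0.0429 = 1.18, about 22%.

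**The case against.** Several stronger conclusions are tempting, and the document does not support them.

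- **That the 6-month effect cannot be estimated.** With the indicator at 1, β2 + 5β3 is a defined contrast. The weakness is that it extrapolates the build-up slope and has no free parameter of its own.
- **That the 12-month effect is biased under any coding.** Coding 1 is unbiased if growth stays on its line or a pure step is held. Coding 0 is unbiased if the effect vanishes at once. Leaving F out is unbiased in every pattern tried.
- **That the primary time point is undefined.** The Analysis plan makes 12 months the tested one and gives a single null hypothesis per outcome. Only the 6-month time lacks a contrast.
- **That there is a false-positive risk.** With no effect in X or F, both codings return zero. The scenarios show loss of effect only.

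It is also fair to say that an indicator defined by having been assigned most naturally stays at 1 after crossover, so the 25% figure belongs to the less likely reading. The 49% figure needs the whole gain to go within six months, whereas the Background presents facilitation as aiming at lasting improvement.

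Finally, a journal article may leave row-level coding to a full analysis plan. That argument has limits here. The article writes out the equation, the indicator, the contrast and the software, and the equation as printed does not match the three states of its own Table 1.

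**Conclusion.** The point stands in bounded form. Model (1) leaves the handling of 8 of 34 wave-quarters open and gives them no parameter. On the natural coding, the 12-month contrast is pulled towards the null whenever the effect falls below its growth line after facilitation ends: about 83% of the log effect is recovered if the gain is held and about 49% if it fades over two quarters. The 6-month effect is then read off an extrapolated line. Under the alternative coding it is fixed at zero, and a held gain is recovered at only about 25% at 12 months.

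These figures form a range over assumed F trajectories. They also assume 2 physicians per site, between-site variance 0.10, an even build-up over the X quarters and a correct linear calendar trend. The full recovery with F indicators depends on the last two assumptions.

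**What to change.** 1. Let the intervention indicator and its slope apply in X quarters only, and add one indicator for the first and one for the second F quarter. At the least, leave F out of the 12-month fit and say so; this protects the 12-month test but leaves the 6-month time without data.
2. Keep β2 + 3β3 = 0 as the primary 12-month test, as the Analysis plan already has it.
3. Define the coefficient of the second F quarter as the 6-month post-intervention contrast.
4. State its limit. By Table 1 the last control quarter is month 15 and the first F quarter is month 21, so no F quarter has a concurrent control and this contrast rests on the linear calendar trend.
5. Settle this before the follow-up data are seen, because the two codings give very different answers.

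The cost is two model terms. The standard error at 12 months rises from 0.0429 to 0.0441 (0.0441/0.0429 = 1.03, about 3%). The much smaller 0.0142 with F coded 0 is no argument for that coding, since it comes from treating post-intervention quarters as control. The 6-month contrast has a standard error of about 0.061 under the same assumptions.

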#### Practice facilitator training and supervision

All practice facilitators received training at the State University of New York at Buffalo Practice Facilitator Certificate Program, a 92-h course with 13 weekly 1.5-h live online classes plus a 40-h fieldwork practicum and 26 h of reflective learning [34]. Twenty-one modules, based on AHRQ’s Practice Facilitation Handbook, cover the full range of topics for trainees to achieve the four core competencies for practice facilitation: data use to drive improvement; interpersonal skills; Health IT optimization; and QI and change management methods (e.g., Plan-Do-Study-Act) [35]. PCIP supplemented the Buffalo program with an additional 20 h of training that focused on increasing knowledge of the ABCS practice guidelines and optimizing the use of the EHR, including creating registries and dashboards, activating clinical decision support systems and other practice change components that correspond to the PF activities in the PCIP QI manual. ABCS toolkits were developed for the practice facilitators to follow that correspond directly to the training content. Three PF managers meet weekly with up to five facilitators each to provide oversight and opportunities for problem solving, identify additional training needs or site specific resources, and review the structured weekly activity reports and monthly narrative reports.

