## Appendix

### Power/effect size analysis

With the pre-specified number of sites (250) and design (wedge design with four strata starting 3 months apart, we investigate the intervention effects under each of the primary hypotheses in Aim 1, that are detectable with at least 80 % power of a two-sided significance test with *α* = 0.05. Conversely, we assess the power to detect effects that are clinically meaningful and realistic.

For each of the four outcomes, we are interested in comparing the proportion of eligible patients in a physician’s panel who meet compliance (i.e., appropriate blood pressure level, appropriate cholesterol level, indication that aspirin was recommended, and indication of referral for smoking cessation) in the third quarter after PF intervention with the compliance proportion at baseline. In particular, we are interested in the difference *d*
_*π*_ = *π*
_3_ − *π*
_0_, where *π*
_0_ is the baseline compliance rate, and *π*
_3_ is the third period compliance rate. The proportions *π*
_0_ and *π*
_3_ will be estimated by *C*
_0_/*E*
_0_ and *C*
_3_/*E*
_3_, respectively, where *C* is the number of patients in compliance and *E* is the number of eligible patients. We will use the model to estimate the difference *d*
_*π*_. However, because of the specific Poisson distributions of the data and the model that we will be using, the treatment effect is more naturally expressed as a ratio rather than a difference: *r*
_*π*_ = *π*
_3_/*π*
_0_.

We conducted the simulations varying the ratio *r*
_*π*_, but for the clarity of interpretation, we also present the effect as a difference *d*
_*π*_. Our goal is to find the *r*
_*π*_ ’ s (and *d*
_*π*_ ’ s) that would allow 80 % power of a two-sided test for significance with *α* = 0.05. We simulate the outcomes based on different assumptions about baseline compliance rates, random effects (which are at the scale of log(*C*)), and patient eligibility numbers. For each set of assumptions, 2000 data sets were generated using the GLMM model given in Eq. (2).

2 $$ \log \left({C}_{jt}\Big|{d}_j\right)=\mu +{\beta}_1t+{\beta}_2{I}_{jt}^{\mathrm{PF}}+{\beta}_3{I}_{jt}^{\mathrm{PF}}\left(t-{s}_j\right)+\gamma {Z}_j+{d}_j+ \log \left({E}_{ijt}\right), $$

The rate ratio *r*
_*π*_ is a function of baseline treatment effect (*β*
_2_) and time-related treatment effect (*β*
_3_) : *r*
_*π*_ = exp(*β*
_2_ + 2*β*

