_3_). For each of the 1000 data sets, we estimated the same model and tested the hypothesis that *β*
_2_ + 2*β*
_3_ (the effect size in the third quarter) was significantly different from 0. The proportion of significant results represented the power of the study under the specific set of assumptions.

For the purposes of simulation, we assumed 63 sites in each stratum, for a total of 252 sites. Preliminary simulations indicated that larger general time trends (*β*
_1_) and larger number of patients in a physician panel both increased power. Based on this, our final simulations included very conservative assumptions of zero growth trend (*β*
_1_ = 0) and average eligibility size (*E*
_*jt*_) of 50 patients per physician at the practice. In the simulation, a general level of *E*
_*j*_ for site *j* was generated from a Poisson distribution of mean 50 × the number of physicians at the site. The value of *E*
_*jt*_ for a particular time period was calculated (and rounded to the nearest integer) as *E*
_*ij*_ + *e*
_*ijt*_, where *e*
_*ijt*_ ~ *N*(mean = 0, sd = 2). For each site *j* during period *t*, log(*C*
_*jt*_) was generated using equation (2). A value *C*
_*jt*_, the number of patients in compliance for site *j* during period *t* was generated from a Poisson distribution with mean *C*
_*jt*_.

Table 4 shows results after varying effect size parameters (*β*
_2_ & *β*
_3_), baseline compliance rate (*π*
_0_), site-level random effect variance (*σ*
_*d*_^2^), and patient eligibility levels (*E*). The current baseline compliance rates for the four measures are 49 % (blood pressure control), 33 % (LDL control for cholesterol), 35 %, (aspirin recommendation), and 20 % (smoking cessation referral). The number of patients that will be eligible in each 3-month period is based on an average physician roster of approximately 1,000 patients. Currently, 30 % of those patients have hypertension, 30 % have hyperlipidemia, and 20 % smoke. If we make a conservative estimate that 25 % of the patients will have an office visit per 3-month period, each eligible category will range from 50 to 75 patients. In Table 4, we use the lowest (most conservative) assumption of 50 patients, which reflects the likely size of the smoking group. At this level of eligible patients, we will have over 80 % power to detect a 2.2 % change, assuming a starting compliance rate of 20 % (increasing from 20.0 to 22.2 %) and between-site variance of 0.10 on the log scale.

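### Model (1) treats counts out of a known denominator as Poisson, so its standard errors are too large, most for blood pressure, unless unmodelled site variation offsets this; the promised provider effect cannot enter the equation

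*Protocol article*

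**What the plan says.** In the Analysis plan (Aim 1), each primary outcome is the number of patients at goal, C_it, at site i in quarter t. The number eligible, E_it, is known and enters as a log offset. The stated model is a log-link mixed model: "we will use a Poisson model with random site and provider within site effects". The test is of β2 + 3β3, two-sided at 5% for each outcome, fitted with lme4. The paragraph states no dispersion parameter or robust variance.

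Equation (1) is indexed by site and quarter only, and its one random term is b_i. The text below it describes a single term that "is a random effect for site *i* with mean 0 and variance" σ_b². (As printed, the subject of that sentence is the offset, but only b_i can be meant.) Equation (2) in the Appendix likewise has only d_j.

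The Appendix explains the ratio scale as chosen "because of the specific Poisson distributions of the data and the model that we will be using". It generates the simulated counts as Poisson and refits the same model. It also gives the rates: "The current baseline compliance rates for the four measures are 49 % (blood pressure control), 33 % (LDL control for cholesterol"), then 35% for aspirin and 20% for smoking cessation.

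**The concern.** A count that cannot exceed a known denominator has binomial, not Poisson, sampling variance. Poisson is a good approximation when the proportion is small, and these proportions are not. The log-scale variance of one site-quarter is 1/(Ep) under Poisson and (1−p)/(Ep) under binomial sampling. The planned standard errors are therefore inflated by an amount that rises with the base rate.

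The single site intercept also leaves nothing to absorb variation of a site from quarter to quarter, or variation between sites in the facilitation effect. If such variation is large it acts in the opposite direction.

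At stake are the p-values and intervals of all four primary tests, each mis-sized by a different amount. The power simulation assumes the same Poisson model for generating and for fitting, so it cannot show the problem. Separately, an analyst cannot follow both the sentence and the equation.

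**Working it through.** **Inputs.** From the documents: four waves 3 months apart with four intervention quarters each (Study design); 63 sites per wave, 252 in all; between-site variance 0.10 on the log scale; 50 eligible patients per physician per quarter, rising to 75 for the larger groups; rates of 20, 33, 35 and 49% (Appendix). Assumed, because the documents do not give them: 1 to 3 physicians per site, and every heterogeneity SD below. The practice-size covariate Z is left out.

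**Formulas.** With X the columns of model (1) (intercept, t, I, I(t−s)), J a matrix of ones and c picking out β2 + kβ3:
- Model covariance per site: V = diag(1/(Ep)) + σ_b² J.
- True covariance per site: T = diag((1−p)/(Ep) + τ²) + σ_b² J + ω² I I′, where τ is the site-by-quarter SD and ω the SD of the site facilitation effect.
- With A = Σ X′V⁻¹X, the model variance is c′A⁻¹c and the true variance is c′A⁻¹(Σ X′V⁻¹TV⁻¹X)A⁻¹c.
- Real alpha = 2Φ(−1.96 × model SE / true SE).

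**Step 1: reproduce the stated power.** The Appendix tests β2 + 2β3. With two physicians per site the formula gives 83.6% for 20.0% to 22.2% (stated: over 80%), 92.6% at 70 patients (stated 92%) and 88.9% for 25% to 27.7% (stated 91%; 90.0% with follow-up quarters included). Refitting in lme4, 400 data sets each, gives 86.5, 93.0 and 91.5%. With one physician per site the first figure would be about 60%. The layout is therefore a fair copy of the plan's own.

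**Step 2: Poisson against binomial, no other heterogeneity (τ = ω = 0), contrast β2 + 3β3, E = 50 to 150.**

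| Outcome (rate) | 1/√(1−p) | SE ratio for the contrast | Real alpha |
|---|---|---|---|
| Smoking (20%) | 1.12 | 1.09–1.10 | 3.0–3.3% |
| Cholesterol (33%) | 1.22 | 1.18–1.20 | 1.8–2.1% |
| Aspirin (35%) | 1.24 | 1.19–1.22 | 1.7–1.9% |
| Blood pressure (49%) | 1.40 | 1.33–1.37 | 0.7–0.9% |

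At E = 100 and 49%, the model SE is 0.0298 and the true SE 0.0220; 0.0298/0.0220 = 1.36 after rounding, and alpha = 2Φ(−2.66) = 0.8%. The lme4 simulation of binomial data gives a ratio of 1.36 and 0.5% rejection at 49%, and 1.06 and 3.7% at 20%.

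**Step 3: power lost.** As an illustration only, take a true ratio of 1.05 at 49% with E = 100. The planned test has power Φ((0.0488 − 1.96 × 0.0298)/0.0220) = Φ(−0.44) = 33%. A correctly specified binomial analysis (SE 0.0216) has Φ(0.0488/0.0216 − 1.96) = Φ(0.30) = 62%.

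**Step 4: the opposite error.** The two errors cancel where (1−p)/(Ep) + τ² = 1/(Ep), that is τ² = 1/E: 0.02, 0.01 and 0.0067 for E = 50, 100 and 150. Above that the SE is too small. For blood pressure:

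| Assumed τ / ω (log scale) | E | Real alpha |
|---|---|---|
| 0.05 / 0.10 | 150 | 3.9–4.5% |
| 0.10 / 0.20 | 150 | 17–19% |
| 0.10 / 0.20 | 75 | 9–10% |
| 0.10 / 0 | 150 | 7.8% |

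The ranges are without and with follow-up quarters. At 0.10 / 0.20, cholesterol (E = 150) gives 13–15% and smoking (E = 100) 8–9%.

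**Step 5: repeated patients.** Eligibility uses a 12-month care window and measurement is quarterly, so patients recur. If 75% keep their status from quarter to quarter (assumed), simulation gives an SE ratio of 1.26 at 20% and 1.54 at 49%. This ignored correlation widens the SE error in the Poisson direction.

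**Step 6: text against equation.** The sentence names site and provider-within-site effects. The equation's counts carry no provider index and its only random term is b_i. A provider effect cannot be estimated from such counts.

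**The case against.** The strongest reply is that the certain error is conservative, so false positives are not at issue, and that an article may leave extra variance terms and robust errors to a fuller plan. The second half is fair: their absence alone would be no finding. But the article does fix the distribution, link, equation, tested contrast and software, and the distribution is wrong for the data it describes. A conservative error of this size still costs power.

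A reader might infer that ignored clustering makes the standard errors too small. The documents do not support that as fact. It needs SDs they do not give; halving the larger pair in Step 4 brings blood pressure back to about 4%, and recurring patients push the other way. Nor is all of that inflation false positives under no effect. If facilitation does nothing at any site, ω is zero, and a site-by-quarter SD of 0.10 alone gives 7.8% (blood pressure), 6.8% (cholesterol) and 5.0% (smoking).

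A reader might also point to facilitators as clusters, from "Three PF managers meet weekly with up to five facilitators each". That implies at most 15 under supervision, not a stated number of facilitators. An assumed facilitator SD of 0.10 gives about 12.5–13.4% for blood pressure, and 0.05 about 3%.

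Fitted proportions above 1 are a lesser matter. Under a normal site effect at 49%, 1.2% of sites exceed 1 at variance 0.10, and 7.7% at 0.25, the upper value considered.

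Finally, it would be wrong to say that the plan intends only a site intercept. The sentence promises more; the equation does not deliver it.

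**Conclusion.** The point holds in two parts that rest on the documents. First, the Poisson variance overstates the standard error of β2 + 3β3 by about 10, 20, 22 and 33–37% across the four outcomes. This depends little on the assumed 1 to 3 physicians per site, and costs most for blood pressure. Second, the sentence and Equation (1) disagree about the random effects.

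A third part is conditional: with large unmodelled site variation the error reverses. Since its size is unknown, the net direction cannot be stated and may differ between outcomes. A claim that the primary tests are anti-conservative goes beyond the documents. The plan should be changed because the size of its tests is not controlled in a known direction, and its power simulation cannot reveal this.

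**What to change.** - Fit a binomial mixed model to C_it out of E_it in lme4 (response cbind(C, E−C)), with random site, site-by-quarter and site-level facilitation effects. Report the ratio and the difference in proportions by marginal standardisation. Alternatively, keep the log link and use site-clustered robust standard errors.
- Align the random effects in the sentence with the equation: delete the provider-within-site wording, or define counts by provider and add the index and the term.
- Re-simulate power from binomial data, for the contrast tested in Aim 1, over a stated range of site-by-quarter and facilitation-effect SDs.
- Treat a facilitator random effect as a sensitivity analysis at most.

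The cost is revised wording, slightly longer fitting and one new simulation. Intervals may widen where real heterogeneity exists. No extra data are needed unless provider-level counts are chosen.
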